## Abstract

**Background:**

Maintaining quality of care in family planning (FP) counselling in low-resource settings is challenging. Job aids can help providers give more accurate and client-specific advice but require a provider to use them effectively and consistently. Marie Stopes International (MSI) have designed the tablet-computer based Digital Counselling Application (DCA), which prompts structured, supportive, client-specific and unbiased FP counselling. We hypothesise that a systematic exploration of clients’ fertility intentions, medical eligibility and preferences will increase their uptake of long acting and permanent methods of contraception (LAPMs).

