Marie Stopes International (MSI) seeks to help women choose a contraceptive method that suits their individual lifestyles and medical needs. In the past, MSI provided FP counselling training for providers that focused on the delivery of information from providers to the clients. More recently, MSI’s training has changed, placing greater emphasis on meeting the clients’ contraceptive needs and preferences. Currently, MSI providers use flipcharts to support their FP counselling sessions. However, providers typically use the flipcharts intermittently and there is substantial variation between providers’ consideration of clients’ circumstances and the suitability of methods recommend. This can result in providers offering unnecessary or an overwhelming number of options to clients, or just offering a subset of suitable options.

Therefore, given the increasingly affordable access to tablet computers, the Medical Development Team at MSI developed a tablet-computer based digital job aid, known as the Digital Counselling Application (DCA). The aim of DCA is to provide a tool that: (1) promotes interaction between providers and clients by forcing providers to ask clients a structured and systematic series of questions and (2) provides the client with a personalised list of recommended methods, based on an algorithm that uses information about the client’s situation, which the provider enters into DCA, removing the need for the provider to do this in their head (and thereby provide advice of varying quality of specificity). Women’s unmet need for modern methods, including LAPMs, is significantly associated with women’s education and empowerment, the quality of client counselling, partner discussions and exposure to media [18, 19].

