### Control

In the control arm, clinics providers will continue to offer the usual provider–client FP counselling service. Typically, this means providers offer an overview of most or all methods before asking the client to select one. However, if providers in control arm clinics have not received MSI’s existing standard training on client-centred counselling within the last 18 months then they will receive refresher FP training. Providers in both the control and intervention arms will have access to their existing job aids, such as posters, diagrams, flipcharts, anatomy models and the WHO contraceptive wheel. Only providers in the intervention arm clinics will have access to and be given training on DCA and the tablets used to run DCA.

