### Sample size

Based on logistical considerations, we assume that we can recruit 75 clients per clinic across 35 clinics during the recruitment period. Based on routine MSI clinic data, we estimate that the primary outcome of LAPM uptake in switchers and adopters is currently typically around 40%. We, therefore, estimate that we will have 80% power to detect an absolute increase in LAPM uptake from 40% to 50.5% (judged by trial researchers and MSI FP experts to be a sufficiently small, clinically important difference for these contexts) at a 5% level of statistical significance, assuming a between-cluster coefficient of variation of 0.2 (based on prior MSI routine data), with 18 clinics in the intervention arm and 17 in the control arm, and 75 clients recruited per clinic [20].

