We will analyse client data based on the original allocation of the clinic that they attended, but we will also conduct sensitivity analyses where we will analyse client data based on how the clinic they attended actually participated in the study (i.e. as either an intervention or control clinic). Prior to the analyses, we will assess the level and pattern of any missingness in outcome or covariate data and investigate the likely causes of missingness. We will conduct complete case analyses of outcomes unless these investigations indicate there is likely to be substantial bias introduced, in which case we will use multilevel multiple imputation methods of analysis [22]. We will make our primary inferences about the statistical significance of the results via formal hypothesis testing. Statistical significance will be at the 5% level based on the (two-sided) *p* values estimated for all outcomes obtained from the covariate-adjusted analyses, as these are likely to have more power and reduced bias (when estimating the treatment effect) than the crude analyses, which will help us to understand how any imbalances in covariates between treatment arms influence the treatment effect [23]. We will evaluate clinical significance based on the effect size estimates and their 95% confidence intervals, with an increase of 10.5 percentage points or more in the primary outcome seen as clinically significant. We will not adjust secondary outcomes for multiple testing. No interim analyses are planned. We will specify our planned analyses in a statistical analysis plan prior to analysis, which will be published with the results.

We will analyse the observation checklist outcomes using survey methods appropriate for the clustered design of the study [24], via the *survey* [25] package in the statistical software R. We will primarily analyse survey checklist outcomes descriptively, either as percentages (categorical outcomes) or as means (continuous outcomes), making inferences about the plausible range of true values for outcomes based on their 95% confidence intervals. We will calculate outcome results from the pooled data and for each country separately, exploring differences in outcomes between countries based on outcome point estimates and 95% confidence intervals.

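### The sensitivity analysis by how clinics participated gives up the randomised comparison and should be replaced by an estimate that keeps clinics as randomised

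*Protocol article*

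**What the plan says.** The protocol article, Statistical analyses, sets the main analysis by allocation: "We will analyse client data based on the original allocation of the clinic that they attended". It then adds sensitivity analyses in which "we will analyse client data based on how the clinic they attended actually participated in the study", with the possible states given as "i.e. as either an intervention or control clinic". The unit is therefore the whole clinic, the classification has two levels, and it depends on conduct after randomisation. The article does not say what would make a clinic count in the other arm.

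Three other places bear on how fully DCA may be used. The Abstract says that job aids "require a provider to use them effectively and consistently". The Background reports that "providers typically use the flipcharts intermittently". The Control section states: "Providers in both the control and intervention arms will have access to their existing job aids". The Intervention section also admits to the trial only providers who pass the knowledge test, so one clinic may hold providers with and without DCA.

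**The concern.** Regrouping clinics by what they did after randomisation is an as-treated comparison. Randomisation balances the 18 and 17 clinics as allocated. It gives no such assurance for the groups formed once some clinics have changed sides. If the clinics that fail to operate as intervention clinics are those with lower (or higher) underlying LAPM uptake, the regrouped comparison shows a difference that DCA did not cause. Readers tend to take agreement between a main and a sensitivity analysis as reassurance, and a biased sensitivity analysis can give that wrongly.

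The analysis can also be uninformative. Where every clinic nominally takes part as allocated, it returns the main result whatever share of sessions used DCA. It then says nothing about the incomplete use that the article's own remarks on job aids make plausible.

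**Working it through.** **Inputs from the protocol (Sample size; Statistical analyses).** Control uptake p0 = 0.40; intervention uptake p1 = 0.505; clients per clinic m = 75; between-cluster coefficient of variation k = 0.2; 18 and 17 clinics; power 80%; the test is "at a 5% level of statistical significance", two-sided according to Statistical analyses.

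**Step 1: reproduce the plan's figure.** Clusters per arm:

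c = 1 + (1.960 + 0.842)² × [p0(1−p0)/m + p1(1−p1)/m + k²(p0² + p1²)] / (p1−p0)²

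- Sampling terms: 0.24/75 = 0.00320 and 0.249975/75 = 0.00333.
- Between-clinic term: 0.04 × (0.16 + 0.255025) = 0.01660.
- Sum 0.02313; multiplied by 7.849 and divided by 0.011025 this is 16.47, so c = 17.47, or 34.9 clinics in total against 35 stated.

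Power is 80.1% at 17.5 clinics per arm, and 80.2% by noncentral t with 33 degrees of freedom. The stated 80% holds, and the same variance assumptions are used below.

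**Step 2: the mechanism by hand, with no true effect.** Assume both arms average 40% and that 3 of 18 intervention clinics, with mean uptake (40 − δ)%, are counted as control.

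- Intervention mean: (18 × 40 − 3(40 − δ))/15 = 40 + δ/5.
- Control mean: (17 × 40 + 3(40 − δ))/20 = 40 − 3δ/20.
- Spurious difference: 0.35δ.

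The between-clinic SD is 0.2 × 40 = 8 points. With δ = 10 (1.25 SD below the mean) the means are 42.0% and 38.5%, a difference of +3.5 points. With δ = 0 it is 0. With δ = −10 it is −3.5.

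**Step 3: simulation over a range, with no true effect.** Clinic uptake was drawn from Normal(0.40, SD 0.08), with 75 clients per clinic and a pooled t-test on clinic proportions, in 40,000 runs per scenario. Two assumptions are not in the protocol: d, the number of intervention clinics counted as control, and r, the correlation between staying in and a clinic's underlying uptake.

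| d | r | Bias, as participated (points) | Type I error, as participated |
|---|---|---|---|
| 1 | 0.5 | +0.8 | 5.6% |
| 1 | 1 | +1.7 | 7.4% |
| 3 | 0 | 0.0 | 5.2% |
| 3 | 0.3 | +1.2 | 6.2% |
| 3 | 0.5 | +2.0 | 8.8% |
| 3 | 0.7 | +2.8 | 12.5% |
| 3 | 1 | +4.0 | 20.9% |
| 5 | 0.5 | +2.8 | 12.4% |
| 5 | 1 | +5.7 | 38.7% |

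Analysis by allocation gave 4.8% to 5.3% in every scenario.

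**Step 4: no clinic changes side.** With d = 0 the two analyses use the same groups and give the same answer. If DCA reached 70% of clients in intervention clinics (assumed) and acted only through use, 10.5 points would appear as 0.70 × 10.5 = 7.35 in both.

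**Step 5: the alternative.** With 3 of 18 intervention clinics not operating as such and no control clinic doing so, the denominator is 15/18 − 0/17 = 0.833. With no true effect the expected numerator is 0, so the expected estimate is 0 whatever r is. If the effect is 10.5 points in operating clinics and none elsewhere, the allocation-based difference is 10.5 × 15/18 = 8.75, and 8.75/0.833 = 10.5. With the denominator taken as fixed, the interval is 1/0.833 = 1.2 times as wide.

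**The case against.** The strongest reply is that this is a sensitivity analysis shown beside an allocation-based main result. That stands. A reader might infer that the trial could declare an inert intervention effective, but the document does not support this, because primary inference rests on clinics as allocated.

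A reader might also infer that clinics select themselves out of DCA. The article does not say so. A clinic could operate in the other arm for administrative reasons unrelated to uptake, and the bias would then be zero. The criterion for participation may well be in the SAP, which is not shown. What the article already fixes is the clinic-level regrouping. Adjustment for country and client covariates may remove part of any selection, but not selection on unmeasured clinic features.

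Dilution from partial use is not an error. The allocation-based difference is the effect of introducing DCA at the level of use achieved, which matters for the roll-out decision in the Discussion.

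Nor does the document support the inference that a null result could not be interpreted. It plans 196 observed sessions with 14 providers, provider interviews about how they use DCA, and staff contact to promote adherence. These are descriptive and do not yield use per clinic, but they are evidence. The exit-interview form is not shown, so the absence of a tablet question cannot be asserted either.

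**Conclusion.** The point holds for the sensitivity analysis only. Regrouping clinics by participation replaces a randomised comparison with a non-randomised one, and with no departures it adds nothing to the main result. For an assumed 3 of 18 clinics moved and no true effect, the bias is 0 to about +4 points if staying in goes with higher uptake, and of the opposite sign if it goes with lower uptake. The number of clinics moved and the strength of the relation are both assumptions, and the simulation is of the crude analysis. The main conclusion of the trial is not affected. This is a modest improvement worth making before analysis.

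**What to change.** Keep allocation as the only basis for inference. Replace the as-participated regrouping with an estimate that uses allocation as the instrument: the cluster-level risk difference divided by the between-arm difference in the proportion of clinics that actually operated as intervention clinics. The SAP should define that status without reference to outcomes. This needs no new data, since the planned analysis already requires each clinic's status. The cost is a wider interval and a stated assumption that allocation has no effect in clinics that did not operate as intervention clinics. If the as-participated result is still shown, label it a non-randomised comparison.

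This estimate does not see non-use within clinics either. Optionally, for clients still to be recruited, record as the last exit-interview item whether a tablet was used, withhold clinic identity from interviewers, and report use per clinic descriptively. Any estimate scaled by client-level tablet use should be labelled exploratory. It assumes that the training does nothing without the tablet, which is doubtful because the Intervention section makes client-centred training part of the package.

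The optional item has costs: client recall is imperfect, coverage is partial because recruitment began in January 2017 (Trial status), and some risk to interviewer blinding remains, since answers from one clinic could reveal its arm for later calls.

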### Qualitative data collection

In-depth interviews will be conducted with a subsample of clients who received FP counselling with the application, whose counselling session was observed and who completed a first telephone interview and consented to being contacted in the future. Purposive sampling will seek to select individuals who received different methods. Clients recruited to the telephone interview will be called again by a researcher, who will seek verbal consent to meet with them and record an in-depth interview. Informed consent will be taken when the client and researcher meet face to face, using a digital recorder to record the client’s consent to be interviewed.

In-depth interviews will be conducted with a subsample of providers who have been trained to use DCA within the intervention arm, who were observed while providing counselling and who are available to undertake an in-depth interview. Purposive convenience sampling will be used to recruit providers, to ensure that providers of all cadres are interviewed. The researcher will seek verbal consent to meet with one provider per clinic and record an in-depth interview. Informed consent will be taken when the provider and researcher meet face to face, using a digital recorder to record the provider’s consent to be interviewed.

A topic guide will be prepared by LAB to structure the interviews. These topic guides will be reviewed in advance by the research team, pre-tested prior to implementation and revised accordingly. With clients, we will explore their experiences and attitudes to FP prior to the counselling session, their experience of being counselled with a provider led by DCA, their acceptance of the FP options recommended by DCA, and their reflection on any changed attitudes to LAPM. With providers, we will explore their attitudes towards good and bad counselling traits, their experience of and response to the training, the acceptability and feasibility of DCA in practice, the perceived impact of DCA on their FP counselling, and discussions around how they use it.

In-depth interviews with clients will take place within 1 month of being counselled with DCA. In-depth interviews with providers will take place after they have used DCA for 3 months. Research assistants fluent in the local language and with qualitative data collection experience will be recruited to the study to collect all telephone data. They will be given training on the study rationale, obtaining consent, confidentiality, use of data collection tools and data protection. These researchers will be supervised by their lead in-country investigator.

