### Design and study setting

We will use a parallel-group, two-arm, cluster randomised controlled trial design to evaluate whether our intervention is superior to the existing treatment (control). We will conduct the study in MSI clinics (formally known as static service delivery centres) across Ethiopia and Vietnam. All clinics in Ethiopia and Vietnam are in urban areas, and typically serve clients with higher incomes than is average for the country. In 2015, 11% of Ethiopian clients and 1% of Vietnamese clients visiting clinics lived below the poverty line of $1.25. Although MSI charges clients for FP services, they have a policy of offering a discount or waiver for clients who cannot pay. Typically, the vast majority of clients self-refer after hearing of the services offered by MSI through social networks.

Clinics are staffed by formally trained clinicians (providers), who are employed and trained by MSI, and the intervention will be delivered by MSI FP providers at the clinic level, with the clinic being the unit of randomisation. A clustered design is necessary because it will not be feasible for clinic providers to switch between delivering the intervention (which involves training) or control treatment to clients. Moreover, this design avoids the risk of contamination between different providers within clinics. In addition to the trial, we will use a structured observational survey to explore how providers are using DCA and counselling clients in the intervention arm. We will also conduct a qualitative study using in-depth interviews with providers and clients to understand their experiences of using and receiving DCA-led FP counselling, respectively, which will also help us understand if and how it can be improved.

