We will also conduct a structured observation survey of provider–client interactions during FP counselling sessions in intervention arm clinics. For this survey, providers will be asked to participate by a researcher, who will seek their written informed consent. The survey will then be carried out in each participating clinic over the course of a day or two, with all clients attending the clinics for FP counselling being asked to participate in the survey by the researcher, who will again seek their written informed consent. An overview of the different quantitative and qualitative components in the trial and their interlinkages is provided in Fig. 2.

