### Provider observation survey sample size

We based the sample size for our provider observation survey on being able to estimate all our proportional outcomes with a precision (95% confidence intervals) no wider than ±10 percentage points (i.e. assuming the least precisely estimable proportion of 0.5), which for an assumed design effect of 2 requires 193 observations. Logistically, we have resources to observe 14 providers, and we, therefore, plan to conduct 196 observations, split between eight providers in Ethiopia and six in Vietnam (14 observations per provider).

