### Randomisation, allocation concealment and masking

For the main trial, all 35 clinics across Ethiopia and Vietnam will be randomised by MSI (ER) simultaneously via a computer program to either the intervention or control arm in a restricted 18:17 (intervention : control) ratio, following recruitment of providers in clinics and after obtaining provider consent. It will, therefore, be possible to conceal treatment arm allocation from providers and clients, but during the trial it will not be possible to blind (mask) either providers or clients to treatment allocation, given the explicit nature of the intervention components (e.g. following treatment allocation, intervention providers will be trained, provided with tablets and use DCA to counsel clients, and clients will be taken through the DCA counselling process). However, data collectors (telephone interviewers) will be blinded to the allocation of clients. For the provider observation survey, we will subsequently select, via simple random selection, eight providers in Ethiopia and six in Vietnam, from all participating clinics.

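### Counselling sessions are observed in the intervention arm only, and some observed clients also supply trial outcomes, so any observer or interview effect is counted as a DCA effect of unknown sign and size

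*Protocol article*

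**What the plan says.** The section on design and study setting says "we will use a structured observational survey to explore how providers are using DCA and counselling clients in the intervention arm". The section on participants, recruitment and consent repeats the restriction: "We will also conduct a structured observation survey of provider–client interactions during FP counselling sessions in intervention arm clinics". The abstract also places this work in the intervention arm. The randomisation section is worded differently and selects "eight providers in Ethiopia and six in Vietnam, from all participating clinics".

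The survey's sample size section states the volume: "plan to conduct 196 observations, split between eight providers in Ethiopia and six in Vietnam (14 observations per provider". The checklist covers desirable provider behaviours and interpersonal conduct. It also records the methods recommended, the method chosen and the session length.

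Under qualitative data collection, client interviewees are those "whose counselling session was observed and who completed a first telephone interview and consented to being contacted in the future". Their timing is given as follows: "In-depth interviews with clients will take place within 1 month of being counselled with DCA".

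The primary outcome and seven secondary outcomes come from the initial telephone interview, and five more secondary outcomes come from the 4-month call. Trial clients are recruited consecutively up to each clinic's target, with no exception for observed sessions.

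**The concern.** A researcher sitting in on a session can change how the provider counsels, how closely DCA is followed and how the client feels about the visit. The checklist items lie close to what the trial measures: methods recommended, method chosen, session length, and how information is explained. A later face-to-face interview that asks clients about their experience and their attitudes to LAPMs could likewise affect continuation, intention to continue and satisfaction at 4 months.

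If both arms had the same exposure, such effects would largely cancel. Here the exposure follows allocation by design, so randomisation cannot remove it. The estimated difference is then DCA plus whatever observation and interviewing do. At stake are the primary comparison, the client-experience outcomes and the 4-month outcomes.

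**Working it through.** **1. Is there overlap?** Three statements together establish it. Observed sessions are in intervention clinics. The qualitative section requires that interviewed clients were both observed and telephoned. The primary outcome section takes its data from that telephone interview. Overlap is therefore certain for the interviewed subsample, whose size is not stated. It is possible for the other observed clients, because consecutive recruitment does not exclude them.

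**2. The plan's own figures.**
- Survey size, with design effect 2, p = 0.5 and half-width 0.10: 2 × 1.96² × 0.25 / 0.10² = 192.07, rounded up to 193. Planned: 14 providers × 14 sessions = 196. This agrees with the article.
- Trial power, with 40% vs 50.5%, m = 75 per clinic, coefficient of variation k = 0.2, 18 vs 17 clinics and two-sided 5%. The variance of a clinic proportion is p(1−p)/m + (kp)².
  - Intervention: 0.505 × 0.495 / 75 + 0.101² = 0.01353.
  - Control: 0.40 × 0.60 / 75 + 0.08² = 0.00960.
  - SE = √(0.01353/18 + 0.00960/17) = 0.0363.
  - Power is 80.2% (noncentral t, 33 df), which agrees with the stated 80%.

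**3. Ceiling on overlap.** Intervention clients: 18 × 75 = 1350. Share: 196/1350 = 14.5%. In a clinic with one observed provider it is 14/75 = 18.7%. Averaging clinic proportions gives the same arm-level figure: 14 × 18.7% / 18 = 14.5%. The control share is 0%.

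**4. Shift in the risk difference.** Shift = share × observer effect. The effect is assumed, since the documents give none. The shift is written as positive but applies equally in the negative direction.

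| Assumed effect in observed sessions | Full overlap (196) | Half overlap (98) |
|---|---|---|
| 5 points | 0.7 points (7% of 10.5) | 0.4 points (3.5%) |
| 10 points | 1.5 points (14%) | 0.7 points (7%) |

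This treats observed clients as no more or less likely than others to be switchers or adopters, the only clients in the primary outcome. It counts observed sessions only. Carry-over to a watched provider's other sessions would add to it.

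**5. Effect on the test.** With no DCA effect, the SE is √(0.0096/18 + 0.0096/17) = 0.0331. At full overlap the two-sided false-positive rate is about 5.5% for a 5-point observer effect and 7.1% for a 10-point effect.

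**6. Cost of leaving observed clients out.** Mean intervention clinic size becomes (1350 − 196)/18 = 64.1. Power by the method in step 2 becomes 79.3%, against 80.2% with them in.

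**The case against.** The strongest reply is that the problem is small and its direction unknown. Much of that stands.

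- A reader might infer that all 196 observed clients are in the trial data. The article shows overlap only for a subsample of unstated size, and it does not fix when observation falls relative to recruitment. The figure of 196 is a ceiling.
- A reader might infer that observation inflates the DCA effect. Nothing in the article shows this. The checklist is not about promoting LAPMs, and the intervention section says DCA is not designed to push them and prompts discussion of side effects. Closer adherence could raise or lower uptake, and a stranger in the room could lower experience ratings.
- A reader might try a larger effect. At 20 points and full overlap the shift would be 2.9 points (28% of target), but 20 points is nearly twice what the whole intervention is powered to detect. Observation alone would need an effect of about 10.5 / 0.145 = 72 points to produce the target difference.
- A reader might conclude that observed clients should be dropped from the primary analysis. That would be a post-randomisation exclusion in one arm, by an event that also required written consent. It would depart from analysis by original clinic allocation.
- The lack of a sensitivity analysis in the article is not itself a fault, because detailed analyses are deferred to a statistical analysis plan that is not shown.

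What remains is the design feature itself: exposure in one arm, with clients who also supply outcomes. Whatever the analysis plan says, that is settled by when and where observation takes place. The randomisation section's wording, read literally, would allow observation in control clinics. The survey's stated purpose of seeing how DCA is used, and the other three statements, point to the intervention arm only.

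**Conclusion.** The point holds as a modest design weakness that is cheap to remove. Observation, and the in-depth interviews drawn from it, occur in the intervention arm only, and at least some exposed clients contribute trial outcomes. Any resulting effect is part of the estimated DCA effect, with sign and size unknown.

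For LAPM uptake, an assumed effect of 5 to 10 points in observed sessions gives a shift of 0.7 to 1.5 points at the 14.5% ceiling, and 0.4 to 0.7 points at half of it. That cannot explain a large result, but it could matter for a borderline one. The experience outcomes may be more sensitive, because they concern the session that was watched. For the 4-month outcomes no figure can be given, since the number interviewed is not stated.

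**What to change.** **Preferred.** In each clinic, hold observation days after its 75 trial clients have been recruited. Telephone observed clients for the qualitative sample only, and amend the interviewee criteria to match. This takes both exposures out of the trial data. The cost is scheduling, plus a small downside: provider behaviour is seen after trial recruitment, not during it.

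**Where observation has already overlapped with recruitment** (recruitment began in January 2017 and was ongoing at submission):
- Flag clients who were observed and those who had an in-depth interview. Selecting interviewees already requires knowing who was both observed and telephoned, so the link should exist.
- Keep all clients in the primary analysis by clinic allocation.
- Pre-specify a sensitivity analysis without the flagged clients for the primary, experience and 4-month outcomes, and report how many were flagged.

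This costs one flag variable and, in the sensitivity analysis, about 1 point of power if all 196 are removed. It does not remove carry-over to unobserved sessions, and removing clients from one arm can bring some selection bias of its own, which is why it should not be the primary analysis.

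**Wording.** Reconcile the randomisation section's statement on where observed providers are drawn from with the intervention-only wording in the design and recruitment sections.
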